**Results:**

Our study was funded in September 2020 by the Department of Defense (W81XWH2010173). We completed the enrollment of our target study population in the October 2022 and are currently working on neuroimaging processing and analysis. We aim to publish the results of our study by 2024. Primary neuroimaging outcome measures will be tested using independent components analysis, seed-to-voxel analyses, and region of interest to region of interest analyses. A repeated measures analysis of covariance (ANCOVA) will be used to assess the effects of active and sham stimulation on sleep variables. Additionally, we will correlate changes in functional connectivity to polysomnography-graded sleep.

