### Study Design and Randomization

This phase 1 clinical trial (ClinicalTrials.gov NCT04953559) will be conducted with a randomized, double-blind, sham-controlled, counterbalanced, crossover design. Participants serve as their own controls as they undergo 2 identical study sessions separated by at least 5 days (ie, washout period). Participants and study personnel who interact with the participants will be blind to the specific condition (active cTBS vs sham) the participant receives during each study visit. Using a prespecified, equally balanced, block randomization procedure, participants will be assigned to the order in which they receive active cTBS and sham stimulation conditions. The randomization list will be generated by a computer random number generator, with the constraint that half of the participants of each biological sex will receive sham first and half will receive the active cTBS first. This design will allow us to examine the intraindividual effects of the active cTBS and establish the superiority of active cTBS compared with sham stimulation in improving PSG sleep outcomes.

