### Power Analyses

During the study design, we conducted a power analysis to determine the sample size necessary to compare mean changes in DMN connectivity before and after cTBS using a within-subjects ANOVA approach. From prior cited work on transcranial magnetic stimulation (TMS) and FC, a total sample of 20 was found to have sufficient power to answer the research questions to include analysis of 2 groups (within-subject active and sham), 2 repeated measurements (before and after TMS), and a correlation between the change in DMN activation and sleep outcome metrics [42,43].

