#### Overnight In-Residence Laboratory Sessions (Visits 2 and 3)

Participants completed 2 overnight in-residence laboratory stays according to a double-blind counterbalanced crossover design, with each session separated by at least 5 days. Figure 2 provides a graphical overview of the in-residence laboratory activities.

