### Analysis Plan

#### FC Changes to the DMN

First-level whole brain connectivity analyses will be undertaken in CONN for each subject at each of the 4 sessions (ie, active prestimulation, active poststimulation, sham prestimulation, and sham poststimulation). This will result in an FC map for each participant at each session, indicating the magnitude and direction of intrinsic correlation between each seed region (eg, lateral parietal cortex of the DMN) and all other voxels in the brain. For our primary analysis, we will estimate the effects of active cTBS on FC within the DMN using multimodal neuroimaging data including resting state FC. Raw NifTI images will be preprocessed using standard functional preprocessing pipelines in CONN [46].

The first-level connectivity maps will be combined in subsequent second-level analyses in CONN to explore the effects of cTBS stimulation on brain connectivity to include (1) independent components analysis, (2) seed-to-voxel analyses, and (3) region of interest to region of interest analyses [44]. Statistically significant differences in FC of the DMN between sham and active conditions will be the minimal important change to confirm the primary hypothesis. Next, PSG parameters measuring sleep stage duration and onsets, arousals, and awakenings will be added as covariates of FC change from before to after stimulation, comparing sham and active cTBS conditions.

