### Experimental Clinical Design Rationale

Double-blind randomized controlled trials are the gold standard for scientific inquiry. Therefore, each participant will serve as their own control in a counterbalanced crossover design. Implementing a crossover design in which every participant receives both active and sham cTBS stimulation permits comparison of intraindividual differences in DMN connectivity and sleep quality parameters, as each participant acts as their own control. Because the goal was to examine the effects of cTBS on individuals with sleep problems, no healthy control samples were recruited or necessary to test our hypotheses. Blinding study personnel to the TMS condition also reduces systematic differences in the administration of the stimulation interventions and ostensibly reduces the influence of expectations about treatment effects.

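### The planned link between connectivity change and sleep names no visit-order term; balanced order protects the mean active-sham contrasts but not this correlation

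*Protocol article*

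**What the plan says.** The protocol article plans an analysis linking functional connectivity (FC) change to sleep in three places.

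- Abstract, Results: "we will correlate changes in functional connectivity to polysomnography-graded sleep".
- Power Analyses: the sample of 20 is said to serve, among other things, "a correlation between the change in DMN activation and sleep outcome metrics".
- Analysis Plan, FC Changes to the DMN: after the main connectivity comparison, PSG parameters "will be added as covariates of FC change from before to after stimulation, comparing sham and active cTBS conditions".

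Order is handled by design. Under Study Design and Randomization, "participants will be assigned to the order in which they receive active cTBS and sham stimulation conditions", with the constraint that "half of the participants of each biological sex will receive sham first and half will receive the active cTBS first". The section on visits 2 and 3 confirms the two-visit layout: "Participants completed 2 overnight in-residence laboratory stays according to a double-blind counterbalanced crossover design". The design rationale relies on this because it "permits comparison of intraindividual differences in DMN connectivity and sleep quality parameters".

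Neither the Primary Outcomes section nor the Analysis Plan names visit, period, sequence or order as a model term. The covariate block of Table 1 does not list it either. Counterbalancing is the only protection against order that the article describes.

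**The concern.** Each person contributes one active and one sham visit, so within a person condition and visit number cannot be separated. For people who had sham first, active minus sham equals the effect plus the visit shift. For people who had active first, it equals the effect minus the shift.

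If sleep differs between the two laboratory nights and pre-to-post FC change differs between the two scan-stimulate-scan sessions, the 20 points separate into two clusters by order. The correlation then partly measures order. No laboratory night before visit 2 is described, so visit 2 is everyone's first PSG night and first stimulation session in the study. A shift is therefore possible, though its size is unknown.

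The trial's hypothesis is that reduced connectivity is the route to better sleep. The FC-sleep link is the planned analysis that speaks to that route, so a link made or hidden by visit order would mislead on it.

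**Working it through.** **The plan's own figure.** The article states that "a total sample of 20 was found to have sufficient power to answer the research questions". It shows no effect size, SD, alpha or power, so 20 cannot be reproduced. For orientation only, at two-sided 0.05 and 80% power, the r detectable with n=20 is tanh[(1.960 + 0.842)/√17] = tanh(0.680) = 0.59. With one covariate removed it is tanh(2.802/√16) = 0.605.

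**Inputs.** From the article: 20 people, two visits each, order split evenly (10:10 if the constraint holds among completers). Assumed: two-sided 0.05, the shift sizes, and the true r.

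**Model.** For person i, the active-minus-sham differences are

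- FC change: D_F = τ_F + s·a_F + e_F
- Sleep: D_S = τ_S + s·a_S + e_S

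Here s = +1 for sham first and −1 for active first. The shift a is in SDs of the difference within an order group, and ρ = corr(e_F, e_S).

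**Mean contrast.** With 10:10 order the mean of s is 0, so the mean of D_F is τ_F and the mean of D_S is τ_S. Order drops out.

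**Correlation.** The mean of s² is 1, so cov(D_F, D_S) = ρ + a_F·a_S, and

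r = (ρ + a_F·a_S) / √[(1 + a_F²)(1 + a_S²)].

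- ρ=0, 0.5/0.5: 0.25/1.25 = 0.20
- ρ=0, 0.75/0.75: 0.5625/1.5625 = 0.36
- ρ=0, 1/1: 1/2 = 0.50
- ρ=0.6, +0.5/−0.5: (0.6 − 0.25)/1.25 = 0.28
- ρ=0.6, 0/0.5: 0.6/√1.25 = 0.54
- ρ=0.6, 0/1: 0.6/√2 = 0.42

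**Simulation** (40,000 trials per setting, n=20, exactly 10:10; Pearson test on 18 df against partial correlation given sequence on 17 df).

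No true link:

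| Shift FC / sleep (SD) | False positives, unadjusted | Adjusted for sequence |
|---|---|---|
| 0 / 1.0 | 5% | 5% |
| 0.1 / 0.5 | 5.3% | 5% |
| 0.25 / 0.25 | about 5.5% | 5% |
| 0.2 / 0.75 | 8% | 5% |
| 0.5 / 0.5 | 14% | 5% |
| 0.75 / 0.75 | 38% | 5% |
| 1.0 / 1.0 | 71% | 5% |

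True r = 0.6:

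| Shift FC / sleep (SD) | Power, unadjusted | Adjusted for sequence |
|---|---|---|
| 0 / 0 | 83% | about 81% |
| 0 / 0.5 | 71% | about 81% |
| 0 / 1.0 | 46% | about 81% |
| +0.1 / −0.5 | 61% | about 81% |
| +0.5 / −0.5 | 18% | about 81% |

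A shift in one measure alone does not raise false positives, but it does cost power, because it adds unexplained spread to that measure.

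**The case against.** **A condensed article may leave model terms to a fuller plan.** This stands in part. The sentence on the link does not list every term, and a document not shown may already contain sequence. A reader might infer that the trial has decided to ignore order; the article does not say so. But it does give the link's outcome, covariates and contrast, and order is in none of them. The analysis as stated can give a wrong answer, and the variable needed to prevent that is already randomised.

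**The large error rates need large shifts in both measures.** This stands. The article gives no shift sizes. FC enters as change within a visit, so a visit shift common to the pre and post scans cancels; only an order effect on the change itself counts. With a small FC shift of 0.1 SD, false positives stay near 5%. Power is less forgiving: 61% at +0.1/−0.5.

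**The form of the model is not fixed.** This also stands. The article does not say whether PSG enters as an active-minus-sham difference or as a per-night value, and a reader should not infer that it prescribes a pooled visit-level model. The figures above are for difference scores. With per-night values order still enters both sides, but between-person variance dilutes the bias.

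**The link does not decide the trial.** Correct. A reader might infer that the main results are at risk. They are not: both confirmation rules are significant active-sham differences, in FC and in sleep, and balanced order leaves those means unbiased. The link is a follow-on step in a pilot, with no success criterion of its own.

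**Conclusion.** The concern holds for the FC-sleep link only. As stated, the link has no order term, and counterbalancing does not protect a correlation of active-minus-sham differences. Order shifts can create or mask a link; nothing in the article shows that they will.

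The size depends on shifts that the article does not give. The false-positive rate runs from about 5% (small shifts, or a shift in one measure only) through 14% (0.5 SD in both) to 71% (1 SD in both). At a true r of 0.6, power runs from 83% with no shift down to 18% with opposite 0.5 SD shifts. These figures assume difference scores, 10 completers per order and a two-sided 0.05 test. The change is worth making because the protection is nearly free. It is not a defect in the trial's main comparisons.

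**What to change.** In the Analysis Plan, under FC Changes to the DMN, state that active-minus-sham FC change will be related to active-minus-sham PSG with randomised sequence as a second-level covariate, that is, a partial correlation given sequence, on 17 df at n=20. If visit-level data are modelled instead, include visit number (2 or 3) with condition and person. Plot the points marked by order. If a fuller plan already includes the term, one line confirming it is enough.

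Cost: one model term, 1 df and no new data. If there are no order effects, power drops by about 2 points (83% to about 81% at a true r of 0.6), and the r detectable with 80% power moves from 0.59 to 0.605. Enrolment is complete, so the remedy has to be made in the analysis, and this one can be.

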#### PSG Analysis

We will assess the effects of active cTBS on sleep and whether participants demonstrated greater sleep quality during their active cTBS session compared with their sham stimulation session. Analyses will be conducted on sleep variables including total sleep time; N1 latency; N2 latency; N3 latency; REM latency; SOL; persistent SOL; SE; WASO; total number of awakenings; spontaneous arousals; wake duration; and stage duration for N1, N2, N3, and REM. Analyses will include repeated measures ANOVA controlling for covariates. Statistically significant difference between sham and active conditions will be the minimal important change to confirm this hypothesis.

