**Objective:**

This trial aims to establish a novel, noninvasive method for treating insomnia through disruption of the DMN with repetitive transcranial magnetic stimulation, specifically with continuous theta burst stimulation (cTBS). This double-blind, pilot randomized controlled trial will assess the efficacy of repetitive transcranial magnetic stimulation as a novel, nonpharmacological approach to improve sleep through disruption of the DMN prior to sleep onset for individuals with insomnia. Primary outcome measures will include assessing changes in DMN functional connectivity before and after stimulation.

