The proposed protocol aims to bridge the gap between cognitive and neuromodulatory interventions to facilitate sleep onset and longer maintenance by temporarily inhibiting the brain FC that is associated with cortical hyperarousal and presleep ruminative cognitions. Our proposed approach will involve using rTMS prior to bedtime to briefly disrupt the strength of FC among cortical regions of the DMN. As we propose to inhibit connectivity within the DMN, we will use continuous theta burst stimulation (cTBS), which induces long-term depression of cortical neural firing following a sustained stimulation period of 40 seconds [40]. Thus, we hypothesize that the application of cTBS to an easily accessible node of the DMN will suppress the local neural activity of that node and propagate inhibition throughout the DMN, thereby reducing ruminative thinking and worry prior to sleep onset. Decreased DMN connectivity is expected to improve sleep quality and quantity. An increase in slow-wave and rapid eye movement sleep stages has been proposed as mechanisms of rTMS in increasing restorative sleep in individuals with insomnia, so polysomnography (PSG) parameters are the primary outcome measures in the outlined protocol [41]. This phase 1 clinical trial will be the first study to investigate the effects of cTBS targeted to the left inferior parietal node of the DMN on objectively measured sleep outcomes.

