**Figure 2 figure2:**

Timeline of the in-residence laboratory testing for the pilot randomized controlled trial. Participants arrive at the lab at 1500 and undergo cognitive testing followed by a preintervention MRI scan. The intervention is administered between 1900 and 2000 and is randomly assigned as either active cTBS stimulation or an identical appearing sham condition. After stimulation, participants complete a postintervention series of MRI scans, followed by a brief cognitive testing battery. At 2200, they are escorted to the sleep lab and PSG electrodes are applied. Lights out occur at 2300 and the participant is provided with an 8-hour undisturbed period for PSG-monitored sleep. Following wake-up at 0700 the next morning, the participant is provided a light breakfast and completes a final battery of cognitive tests. This procedure is repeated on separate weeks for the active cTBS and placebo conditions. cTBS: continuous theta burst stimulation; MRI: magnetic resonance imaging; PSG: polysomnography.

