#### PSG Recording

Participants slept undisturbed in a light- and temperature-controlled private bedroom while continuously monitored by a trained technician with a Nihon Kohden JE-921 PSG recording system using standard 10-20 electrode placement. Data from PSG were scored using Polysmith software according to the standard Rechtschaffen and Kales approach by a trained and certified sleep technician who was blind to the participant’s condition and status. The primary outcome metrics include sleep onset latency (SOL), latency to N1, N2, N3, and REM, total sleep time (TST), sleep efficiency (SE), wake after sleep onset (WASO), and number of awakenings and arousals, as well as time and percentage of time spent in each sleep stage.

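### A significant sham-active difference is said to confirm the sleep hypothesis, but 16 sleep variables are listed with none named as deciding, and the article disagrees on whether PSG, FC or both are primary

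*Protocol article*

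**What the plan says.** **The sleep decision rule.** PSG Analysis lists its variables in two runs: "Analyses will be conducted on sleep variables including total sleep time; N1 latency; N2 latency; N3 latency; REM latency; SOL; persistent SOL; SE; WASO", then "total number of awakenings; spontaneous arousals; wake duration; and stage duration for N1, N2, N3, and REM". The analysis is a repeated measures ANOVA with covariates. The section ends: "Statistically significant difference between sham and active conditions will be the minimal important change to confirm this hypothesis". Study Design and Randomization states that the design will serve to establish superiority of active stimulation in improving PSG outcomes.

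**A second PSG list.** PSG Recording has its own list, labelled primary: "The primary outcome metrics include sleep onset latency (SOL), latency to N1, N2, N3, and REM, total sleep time (TST), sleep efficiency (SE". It goes on to WASO, awakenings, arousals, and both time and percentage of time in each stage.

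**What is primary.**
- Abstract, Objective: "Primary outcome measures will include assessing changes in DMN functional connectivity before and after stimulation".
- Introduction, Overview: "polysomnography (PSG) parameters are the primary outcome measures in the outlined protocol".
- Table 1: DMN connectivity and PSG sleep both stand under primary outcomes.
- The outcome section after Data Management carries FC alone in its heading, and FC Changes to the DMN ties the primary hypothesis to an FC difference.
- Power Analyses sizes the trial on DMN connectivity. Sleep enters only through a correlation with the change in the DMN.

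**The concern.** A rule that says when a hypothesis is confirmed must say which result decides. This one is attached to 16 variables and leaves that open. Someone applying it after the data are in could point to whichever variable reached significance and report the sleep hypothesis as confirmed, within the letter of the published plan.

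The unsettled primary outcome adds to this. If connectivity is positive and sleep is not, or the reverse, the article contains a sentence that supports presenting either one as primary. At stake is the trial's claim that a single stimulation improves sleep.

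**Working it through.** **Plan's own figure.** The only design number is N = 20. It cannot be reproduced, because no alpha, power, effect size or SD is given. The check below does not depend on it, except that the simulations use n = 20.

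**Step 1. Count the variables.**
- PSG Analysis: TST (1), latencies to N1, N2, N3 and REM (4), SOL (1), persistent SOL (1), SE (1), WASO (1), awakenings (1), arousals (1), wake duration (1), durations of N1, N2, N3 and REM (4). Total 16.
- PSG Recording: SOL (1), four latencies (4), TST (1), SE (1), WASO (1), awakenings (1), arousals (1), time in four stages (4), percentage in four stages (4). Total about 18.
- The second list adds stage percentages and omits persistent SOL and wake duration. Both lists are open-ended.

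**Step 2. Overlap.** The caption of Figure 2 fixes the recording window: "the participant is provided with an 8-hour undisturbed period for PSG-monitored sleep". That is 480 minutes, so SE = TST/480, the same test as TST. The four stage durations sum to TST. If wake duration means all wake time in the window (an assumption, since it is not defined), it equals 480 − TST and is the same test again.

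**Step 3. Chance of at least one significant difference when there is no effect.** Assumption: two-sided alpha 0.05 per variable, any one variable sufficing, no adjustment.
- Independent tests: 1 − 0.95^k. For k = 16: 1 − 0.440 = 0.560. For k = 18: 1 − 0.397 = 0.603.
- One direction only (0.025 per test), k = 16: 1 − 0.975^16 = 1 − 0.667 = 0.333.
- Correlated tests: simulated paired t tests, n = 20, 16 variables with a common correlation. The correlations are assumptions.

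| Correlation | Any difference (nominal 5%) | One direction only (nominal 2.5%) |
|---|---|---|
| 0 | 56% | 33% |
| 0.3 | 48% | 25% |
| 0.5 | 39% | 20% |
| 0.7 | 28% | 14% |
| 0.9 | 15% | 8% |

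The two-sided column is about 3 to 11 times its nominal rate (0.15/0.05 = 3; 0.56/0.05 = 11.2). The one-direction column is about 3 to 13 times (0.08/0.025 = 3.2; 0.333/0.025 = 13.3).

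**Step 4. Under a repaired rule.** With one named variable the rate is 5%. With a Bonferroni threshold of 0.05/16 = 0.003125 it is 1 − (1 − 0.003125)^16 = 0.049 if independent, and about 0.015 at correlation 0.9. With 20 participants, the standardised paired effect detectable with 80% power rises from 0.66 at alpha 0.05 to 0.96 at 0.003125.

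**Step 5. The primary outcome, side by side.** The Introduction gives PSG. The FC outcome heading and the primary hypothesis in the analysis plan give FC. Table 1 gives both. No sentence says whether one success is enough or both are needed.

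**The case against.** Several stronger readings are tempting, and the document does not support them.

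- *That a false confirmation is more likely than not.* This needs near-independent tests. The variables overlap heavily, and at correlations of 0.5 to 0.7 the two-sided figure is 28% to 39%, lower still if only improvement counts. Inflated well above nominal is supported; likely is not.
- *That the plan states an any-one, unadjusted rule.* It does not say how many variables must differ, nor whether p values are adjusted, and an unseen SAP may say so. This stands as a caution on wording. It does not remove the point, because the article itself publishes a confirmation rule and nothing in it excludes the loose reading.
- *That no direction of benefit is given.* An overall direction is given: PSG Analysis asks about greater sleep quality, and the hypothesis is improvement. What is missing is a direction per variable where benefit is ambiguous, such as N1 or N2 duration.
- *That every statement on the primary outcome conflicts.* The abstract's wording on FC is not exclusive, and PSG Recording fits Table 1. The real conflict is between the Introduction, which gives PSG, and the FC outcome heading and primary hypothesis, which give FC, with no co-primary rule to join them.
- *That the two PSG lists contradict each other.* Both are open lists, so this is looseness. It matters because one of them is labelled primary.

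It can also be said that this is a small phase 1 pilot with exploratory aims, which the article acknowledges. That would excuse a descriptive analysis. It sits poorly with a rule for confirming a hypothesis and an aim of establishing superiority.

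**Conclusion.** The point holds. The published rule for the sleep hypothesis does not identify the deciding result among 16 listed variables, and the article does not settle which outcome domain is primary. Under the any-one, unadjusted reading, the false-confirmation rate exceeds nominal in every scenario examined: 15% to 56% against 5% two-sided, and 8% to 33% against 2.5% in one direction. These ranges assume alpha 0.05 two-sided per variable and a common correlation between 0 and 0.9; the article gives neither. Where the truth lies in the range cannot be determined from the document, but overlap among the variables makes the independent-test figure an upper reference rather than an estimate. The inconsistency over the primary outcome needs no assumption. It governs the trial's main efficacy claim for sleep and should be corrected.

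**What to change.** 1. State one outcome hierarchy and carry it through the abstract, the Introduction, Table 1, PSG Recording, the FC outcome section and the analysis plan. Either FC is primary with PSG key secondary, or the two are co-primary with a stated rule, including the alpha split if success on either one is enough. The choice is the sponsor's.
2. Name one deciding PSG variable with its direction of benefit, or apply Holm to the listed set, which must then be a closed list. With 20 participants, naming one variable costs far less power (Step 4).
3. Report the remaining PSG variables as supportive, with 95% confidence intervals, and give a direction of benefit wherever one is claimed.
4. Use one PSG list in PSG Recording and PSG Analysis. Define wake duration, and drop entries that repeat TST.
5. If PSG is tested only after FC, also name one deciding FC contrast. The analysis plan lists three FC families (independent components, seed-to-voxel, region-to-region), and a sequence that starts from an undefined test does not control error.

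**Cost.** Wording only, with no new data. Single PSG results outside the named variable or the adjusted set lose confirmatory status. Enrollment ended in October 2022, and the article does not say whether condition labels are still closed. If they have been opened, the choice must be disclosed as post hoc.
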